### Participants, schedule and timelines

We will inoculate healthy non-smoking adult participants with a well-characterised, fully sequenced penicillin-sensitive pneumococci and observe them for the development of pneumococcal carriage up to 14 days post inoculation. Study discharge will occur on day 20.

Study visits must take place according to the proposed schedule to ensure participant safety. This will be clearly explained to the participants during recruitment and consent. If a participant is unable to comply, they will not be recruited (Participant flow chart -
Figure 1).

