### Safety during colonisation

A three-day course of amoxicillin and a digital thermometer will be given on the day of inoculation. These will be carried by the participants for immediate treatment after phone consultation should the participant develop any symptoms as described on the participant safety advice leaflet
^14^. Participants will be required to make text message/phone contact with a specified member of the research team before 1200 hrs every day for 7 days post-inoculation
*regardless of whether they have symptoms or not*. Should they not make contact by the specified time, a member of the research team will contact the participant. If no contact is made, then a prior defined ‘secondary contact’ will be telephoned. During the post-inoculation period, participants will have access to a 24/7 on-call telephone service until the end of the study.

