### Termination of carriage

All study participants who are nasally colonised with pneumococcus at the end of the study will be asked to take oral amoxicillin 500mg three times daily for 3 days. This will be communicated at visit 7, or by telephone in the unlikely event of only visit 7 samples (day 14) showing carriage.

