### Safety considerations and assessment

***Study design to ensure safety.*** Safety is paramount in human infection studies. While the risk to individuals of developing any infection is very low (40% Malawian adults experience natural colonisation at any time, and the incidence of invasive disease is 20/100 000 patient years
^5^), the study is designed to ensure any risk is minimal by appropriate:

Study team selection and rigorous training in human challenge proceduresStudy design with staggered recruitment approach (sample size and dose)Careful serotype selection and dosing based on 10 years of LSTM experienceParticipant selection and exclusion criteria as detailedParticipant education through a participant information sheet (provided)Rigorous safety procedures including daily monitoring and providing participants with a thermometer and a course of amoxicillin tablets in case of emergency
^14^
24-hour emergency telephone contact with researchers, including close individual daily monitoring, and access to hospital facilities and prompt treatment if requiredTo further mitigate risk, participants will be provided with accommodation at the Grace Bandawe Centre for three nights immediately following nasal challenge. If a participant determines that it is not possible to stay at the Grace Bandawe Centre for three nights then a pragmatic approach to further study procedures will be taken. If the participant can demonstrate that they remain readily available by phone and accessible with transport, this need not affect the procedure. Twice daily checks could replace the resident period. In the Liverpool CHIM there is no resident period at all. If, however, the participant absconds or is intending to be uncontactable, then participation in the study will be stopped and antibiotics offered as at the end of the protocol.

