We will schedule inoculations such that participant monitoring (to day 20) is completed at each pneumococcal dose (20,000 and 80,000) prior to escalation. The feasibility study research investigators [name], [name], [name] and [name] have successfully worked together to safely deliver pneumococcal CHIM studies in Liverpool and will transfer this knowledge and experience to MLW. No episodes of pneumococcal infection or serious unexpected serious adverse reactions (SUSARS) have occurred in any of our participants whether they had no carriage, natural carriage or experimental carriage. We will transfer and rigorously implement the Standardised Operating Procedures to ensure safety for Malawian participants.

***Participant safety procedures.*** We will provide all participants with a safety information sheet
^14^. This sheet classifies symptoms into mild, moderate and severe. We will take a proactive approach for participants, with daily contact throughout the study and enquiry about development of any symptoms. We will also encourage participants to report development of any symptoms with 24-hour medical cover throughout the study visit schedule. In the event of illness, we will apply standardised operating safety procedures for participants. The research team will pay for any costs associated with these procedures and participants will incur no out of pocket expenses.

*Mild illness*

Mild illness is defined as development of any new symptom that is of concern to the participant during the study period. These may include mild coryzal symptoms such as blocked or runny nose. Participants will be encouraged to contact the research team by telephone within office hours. During the telephone assessment participants will be screened for potentially concerning moderate and severe symptoms. If there is any concern, participants will be invited to the research clinic for a detailed clinical assessment by one of the study doctors. The assessment will be fully documented within study records including rationale for any treatments and/or required modifications to study procedures.

*Moderate Illness*

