Moderate illness events are defined as fever with temperature >37.5°C, shivering, headache, new rash, drowsiness, cough, new earache and or new eye infection. Participants will be clearly instructed to call the research team at any time of the day upon development of these symptoms. During the telephone assessment participants will be screened for severe symptoms and requested to attend either the research clinic (office hours) or Mwaiwathu hospital (outside of office hours) for medical assessment. If severe symptoms are identified on telephone assessment, participants will be asked to take antibiotics from their supplied emergency pack and attend Mwaiwathu hospital. Study doctors will assess the participants at either the research clinic or Mwaiwathu and offer appropriate treatments. The assessment will be fully documented within study records including rationale for any treatments.

*Severe illness*

Severe illness events are defined as any symptoms that cause serious concern to participants following inoculation. We have purposefully taken a conservative approach to encourage participants to seek early medical advice and treatment if they are concerned. Participants will be counselled as to what symptoms the study team may be particularly concerned about during the consent process
^24^. These would include any potential symptoms of sepsis. In the event of severe illness, participants are requested to start taking the provided emergency antibiotics, directly attend Mwaiwathu hospital and contact the study team. A study doctor will attend the patient in Mwaiwathu and offer appropriate treatments. The assessment will be fully documented within study records including rationale for any treatments.

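### The daily check-in and its missed-contact call-back are written for 7 days, although the protocol commits to daily contact throughout a study that ends on day 20

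*Protocol article*

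**What the plan says.** Safety during colonisation sets the operational rule. Participants make contact "before 1200 hrs every day for 7 days post-inoculation", with or without symptoms. The follow-up is tied to that deadline: "Should they not make contact by the specified time, a member of the research team will contact the participant". If this fails, a secondary contact named in advance is telephoned. The same section keeps a 24/7 on-call line open to the end of the study.

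Safety considerations and assessment states the wider commitment. Under Participant safety procedures, the team will be proactive, "with daily contact throughout the study and enquiry about development of any symptoms". The list of risk-reducing measures under Study design to ensure safety has "including close individual daily monitoring" with no end day, and the text after it says monitoring to day 20 is completed at a dose before escalation. Participants, schedule and timelines gives the end point: "Study discharge will occur on day 20".

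Two other provisions bear on a participant who falls silent. Within the item on three nights' accommodation the protocol says: "If, however, the participant absconds or is intending to be uncontactable, then participation in the study will be stopped and antibiotics offered". The Missing data paragraph of Statistical analysis notes that secondary contact details are held for every participant.

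**The concern.** The same safety measure appears with two durations. The specific rule, which has a deadline, a call-back and a second call, covers week 1. The general promise covers the whole study. Staff working from the specific rule could reasonably stop active daily contact after day 7. Staff working from the general promise would carry on, but would find no instruction on what to do when a contact after day 7 goes unanswered.

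This matters because of when carriage is treated. Termination of carriage asks participants who are colonised to take amoxicillin, and on timing says: "This will be communicated at visit 7, or by telephone". Visit 7 is on day 14. A carrier found on day 2 or day 7 may therefore still be colonised and untreated on days 8 to 13, unless carriage has cleared or the emergency pack has been used. A call-back sequence helps most when someone is too unwell to call, and it should be clear whether it still applies then.

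**Working it through.** No figure in the plan needs reproducing. The check is a comparison of texts and a day count.

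**Texts side by side**

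| Element | Who acts | Duration stated | Section |
|---|---|---|---|
| Check-in before noon | Participant | 7 days | Safety during colonisation |
| Call-back, then secondary contact | Team | None of its own; triggered by missing the check-in time | Safety during colonisation |
| Daily contact with symptom enquiry | Team | Throughout the study | Participant safety procedures |
| Daily monitoring | Team | No end day | Study design to ensure safety |
| 24/7 line | Participant | To end of study | Safety during colonisation |
| Discharge | – | Day 20 | Participants, schedule and timelines |

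The call-back depends on a specified time, and that time exists only for the 7-day check-in. Its written reach is therefore days 1 to 7.

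**Day count**

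- Days after the check-in ends, up to discharge: 20 − 7 = 13 (days 8 to 20).
- Visit 7 is on day 14 (Statistical analysis, Feasibility). Visit 8 is assumed to be on day 20: Inoculation ends participation at visit eight, discharge is day 20, and Figure 1 is not shown.
- Between-visit days: 13 − 2 = 11, of which 13 − 7 = 6 (days 8 to 13) fall before visit 7.

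**What the count means under each reading**

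- If the commitment to daily contact throughout is followed, 0 of the 13 days lack scheduled enquiry. The call-back sequence is still not written for the 11 between-visit days.
- If the 7-day rule is followed alone, up to 11 of the 13 days have no scheduled active enquiry.

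**Other cover on days 8 to 20**

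- Depends on the participant acting: the 24/7 line, the symptom log given out at inoculation, and the moderate-illness instruction ("Participants will be clearly instructed to call the research team at any time of the day upon development of these symptoms").
- Does not depend on the participant calling first: visits 7 and 8, collection of adverse events, the absconding provision, and the secondary contact details on file.

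**The case against.** The strongest reply is that there is no contradiction. The 7-day rule says what participants must do, the commitment to daily contact says what the team will do, and both can be followed at once. A structured check-in concentrated in week 1, beside three nights' residence, is a defensible design. A journal article may also leave call-back detail to standard operating procedures and the safety leaflet, neither of which is shown.

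Much of this stands. The sections are reconcilable, and a reader who inferred that follow-up stops on day 7 would go beyond the text. What does not stand is that the matter is only omitted detail. The article itself gives the deadline, the duration and the call-back, and the duration it gives is shorter than its own commitment. Nothing says the call-back applies to the later team contacts.

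Three stronger readings are tempting and are not supported:

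- A reader might infer that the team has no stated step for a silent participant after day 7. The absconding provision carries no day limit: it stops participation and offers antibiotics. It sits in the accommodation item and sets no time trigger, so it does not replace a call-back sequence, but it is a stated step.
- A reader might infer that only the week-1 sequence would reveal loss of contact. An unanswered daily team contact, or a missed visit, would reveal it too.
- A reader might measure the gap by the days that carriers spend untreated before visit 7. Those days follow from an endpoint that needs the day-14 nasal wash, and they would exist with a perfect call-back sequence.

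**Conclusion.** The point holds as a minor inconsistency in a safety procedure. The check-in and the call-back triggered by missing it are limited to 7 days, against a commitment to daily contact throughout and monitoring to day 20. The window concerned is 11 between-visit days, assuming that visit 8 falls on day 20. On those days the call-back sequence is not written to apply. Whether scheduled enquiry is also absent depends on which section staff follow, with a range of 0 to 11 days.

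The documents do not show that any contact would in fact be missed, and the cover listed above is real. The carriage endpoint, the decision rules and the timing of escalation do not change. The case for acting is that the text fixes a shorter limit than the protocol's own commitment, in a challenge study of healthy volunteers, and that correcting it costs little.

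**What to change.** Amend Safety during colonisation so that daily contact, the team call-back and the secondary-contact call run to discharge on day 20, in line with Participant safety procedures. Apply it to all remaining participants in every cohort, whatever their carriage result, so that contact frequency says nothing about allocation to the blinded clinical team and participants. Record the contact window actually used for the eight participants already inoculated at 20,000 CFU (Study status).

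The cost is up to about 11 brief texts or calls per participant by existing staff, and none extra if daily contact throughout is already practised. Ignoring replacements for withdrawals:

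- Expected path, with 20,000 CFU ending at eight participants and 80,000 CFU completing with 8 + 4 = 12: 12 remain, so 12 × 11 = 132 contacts.
- Fewest, with 20,000 CFU completing at 12: 12 − 8 = 4 remain, so 4 × 11 = 44.
- Most, with the maximum of 36 recruited: 36 − 8 = 28 remain, so 28 × 11 = 308.

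The change also needs approval by the ethics committee and the sponsor (Amendments).

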### Termination of carriage

All study participants who are nasally colonised with pneumococcus at the end of the study will be asked to take oral amoxicillin 500mg three times daily for 3 days. This will be communicated at visit 7, or by telephone in the unlikely event of only visit 7 samples (day 14) showing carriage.

### Immunological assays

•
*Antibody titres* – measurement of pneumococcal-specific protein and polysaccharide antibodies will be conducted on nasal wash, salivary and serum samples using ELISA as previously reported
^15^. This will allow us to test the existing LSTM protocols for the identification of potential antibody correlates of protection against pneumococcal colonisation.

•
*Cellular responses* – measurement of pneumococcal-specific memory B and T cells will be performed on peripheral blood and nasal samples using flow cytometry and ELISPOT as previously reported
^16,
17^. This will allow us to test the existing LSTM protocols to identify potential cellular correlates of protection against pneumococcal colonisation.

•
*Cytokine profiles* – measurement of cytokines will be done on nasosorption and serum samples using multiplex bead array as previously reported
^18^. This will enable us to identify potential soluble marker correlates of protection against pneumococcal colonisation.

•
*Host transcriptomic analysis* – measurement of host nasal mucosa transcriptomic profile will be done using RNA sequencing (RNAseq) on nasal cells and peripheral blood as previously reported
^16^. This will allow us to establish protocols for characterising potential nasal or blood transcriptomic signatures associated with protection or susceptibility to pneumococcal carriage.

•
*Microbiome profiles* – measurement of microbiome profiles will be done on throat swabs and nasal washes using next-generation sequencing and metagenomic analysis as previously reported
^18^.

### Sample size justification

This is a feasibility study that transfers a proven existing technique therefore we have not formally calculated power to detect the carriage rate. The study protocol and sample size are based on our previously published study demonstrating 50% nasal carriage at the 80,000 CFU dose in Liverpool, UK
^13^. This feasibility study is designed to determine if experimental pneumococcal nasal carriage is possible in the Malawian setting.

The primary endpoint is the occurrence of pneumococcal colonisation determined by the presence of pneumococcus in nasal wash samples at any time point post inoculation detected using classical microbiology.

### Statistical analysis

The reporting of this study will be prepared in accordance to the CONSORT 2010
^19^ guidelines. The full statistical analysis plan is provided as extended data
^20^. A CONSORT diagram will summarise participant screening, enrolment, randomisation, inoculation, withdrawals, follow-ups and analysis. All continuous data variables will be summarized using the following descriptive statistics: N (size of relevant analysis population), n (size of analysis population without missing values), mean, standard deviation, median, 25
^th^ percentile value, 75
^th^ percentile value and interquartile range, minimum and maximum. The proportion of observed levels will be reported for all binary and categorical measures. When appropriate, corresponding exact, binomial 95% confidence intervals (CIs) for proportions will be included.

***Timing of analyses.*** The primary feasibility endpoint of nasal colonisation will be assessed at least 2 times and up to 5 times given the adopted dose escalation design (
Figure 2), after all participants from each inoculation batch have concluded visit 7 (d14). All other feasibility analyses will be conducted at the completion of the study. Safety endpoints will be monitored continuously throughout the study and will be summarised at the completion of the study.

***Missing data.*** Due to the close monitoring of study participants, with secondary contact details available for every participant, few missing data are anticipated. Still, study participants may withdraw from the study, and missing data may originate due to a variety of reasons.

For the primary feasibility endpoint, data will be available for as many participants as given by the study design from
Figure 2 since an alternative participant will be recruited in the case of withdrawal of a participant. Participants missing study visits so that no day 2, 7 or 14 data is available will be withdrawn from the study and their data excluded from data analysis. A new participant will be recruited in such a case and this new participant will be allocated to the same pneumococcus / sham inoculation as the participant ID for the withdrawn participant was randomised to. The primary feasibility endpoint will be assessed, at each of the five analysis time points using colonisation results data from all participants that are required for that stage’s analysis and that have completed visit 7 (d14). Other analyses are primarily descriptive or make use of censored data techniques, so that no advanced missing data methods will be used in these analyses. Data collection forms are provided in extended data
^21^. 

***Statistical significance and multiple testing.*** Success (feasibility) of the study will be decided according to the decision rules stated on
Figure 2.

Success (safety) of the study will decided by decision of the DSMB & TC upon revision of each SAE and SUSAR. For this reason, no formal null hypothesis significance testing will be performed for the main analysis and no multiple testing adjustment will need to be made.

For secondary analyses, statistical significance is defined as p<0.05, but effect sizes / parameter estimates, exact p-values and confidence intervals will be stated. While we will report on statistical significance, results will be presented and discussed in accordance with recent guidance
^22^.

***Technical details.*** All analyses and figures will be performed using the R environment (v.3.5.3 or later) for statistical computing and graphics and associated packages
^23^.

***Feasibility.*** The primary analysis aims to establish feasibility of the Malawi CHIM: does one of the three doses (20,00, 80,000, 160,000 CFU) lead to ≥50% nasal colonisation?

To assess this, the decision algorithm specified in the study design (
Figure 2) is followed and no statistical analysis is required. However, we will complement this with a number of descriptive and secondary analyses: For each inoculation dose used in the study, we will estimate colonisation (by serotype 6B) rates and compute 95% exact, binomial confidence intervals. We will also compute this for participants inoculated with the sham, saline solution. If more than 1 dose is used in the study, we will plot the estimated colonisation rate against inoculation dose for a crude estimate of the dose-response curve. For each inoculation dose, we will also plot time curves of colonisation rates at visits 0 (d-5), 4 (d2), 6 (d7), 7 (d14). We will also use lytA qPCR to assess nasal carriage by
*Streptococcus penumoniae*. We will repeat all analyses using this method of carriage detection. Further, for the qPCR results, we will estimate average carriage densities and associated 95% confidence intervals for each challenge dose. If more than one dose is used, we will also plot individual carriage densities against inoculation dose for a crude estimate of the carriage density dose response curve. We will estimate the lower limits of detection and quantification for the qPCR data, then use censored data techniques to account for the uncertainty associated with values below these limits.

We will compile a summary table for demographic (age, sex), baseline physiological (pulse rate, oxygen saturation on room air, systolic blood pressure, diastolic blood pressure, tympanic body temperature, height, weights, BMI, baseline carriage of
*S. pneumoniae* other than serotype 6B) and baseline immunological variables. Baseline physiological and immunological variables are those measured at the inoculation visit or for which the sample was taken at the inoculation visit (prior to the inoculation). Analogous tables will be compiled for the assessments made at visits 2–8.

***Safety.*** AEs, SAEs, SUSARs are monitored throughout the study and any decision to stop the trial is taken by the TSC in consultation with the DSMB. At study end, AEs, SAEs and SUSARs will be listed by type and by inoculation group (sham,
*Streptococcus pneumoniae* 20,000 CFU, 80,000 CFU, 160,000 CFU) and we will also stratify these lists by sex and age band. Symptoms reported by study participants will also be listed, including sore throat, coryzal symptoms, earache, feverish, cough, headache, new rash and/or other. The reasons why any participants are withdrawn from the study and/or excluded from analysis will also be listed. 

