### Study hypothesis

That inoculation of Malawian volunteers with 80,000 cfu/naris will safely result in nasopharyngeal carriage in ~50% of participants as it has done in Liverpool.

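### The rule that excludes participants with no day 2, 7 or 14 data is not limited to the carriage analysis, so read literally it could remove inoculated people from the end-of-study adverse-event and symptom listings

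*Protocol article*

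**What the plan says.** Under Statistical analysis, Missing data, the protocol article starts from the carriage endpoint: "For the primary feasibility endpoint, data will be available for as many participants as given by the study design from" the dose-escalation figure, because anyone who withdraws is replaced. It then says that participants whose missed visits leave no day 2, 7 or 14 data "will be withdrawn from the study and their data excluded from data analysis". For the replacement, "this new participant will be allocated to the same pneumococcus / sham inoculation as the participant ID for the withdrawn participant was randomised to". The same paragraph ends on the remaining analyses: "Other analyses are primarily descriptive or make use of censored data techniques, so that no advanced missing data methods will be used in these analyses".

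Under Statistical analysis, Safety, adverse events, serious adverse events and SUSARs are to be listed by type and inoculation group, and participant-reported symptoms are to be listed as well. That text adds: "The reasons why any participants are withdrawn from the study and/or excluded from analysis will also be listed". No population is named for these listings, neither completers nor everyone inoculated.

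Safety is the third study aim, and the study hypothesis is that the 80,000 CFU dose "will safely result in nasopharyngeal carriage in ~50% of participants".

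**The concern.** Excluding and replacing a participant with no nasal-wash result is a workable rule for a carriage denominator, since without a wash carriage cannot be classified. It does not suit safety. A person who was inoculated and then left still contributes exposure, and possibly symptoms, whether or not a wash was obtained.

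The exclusion sentence refers to the participant's data and to data analysis in general. An analyst who follows it to the letter could leave inoculated people out of the non-serious adverse-event and symptom listings. The same-allocation replacement would then make the dose group look complete. Leaving early need not be independent of feeling unwell, although the documents do not show that it is related. With at most nine challenged participants planned per dose, one omitted person can change the picture, including the contrast with sham that the design was given so that challenge effects can be told apart from study conditions.

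**Working it through.** **1. Group sizes (Figure 2 caption; Recruitment target).** Each of the first two doses has up to 8 + 4 = 12 participants, of whom 6 + 3 = 9 are challenged and 2 + 1 = 3 are sham. The third dose has 12 (9 challenged, 3 sham). Total: 3 × 12 = 36, which reproduces the stated maximum, with 27 challenged and 9 sham.

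**2. Whom the rule reaches.** The trigger is "Participants missing study visits so that no day 2, 7 or 14 data is available will be withdrawn from the study and their data excluded". Days 2, 7 and 14 are counted from inoculation, so someone caught by missing these visits has already been inoculated. The trigger can be read in two ways:
- All three samples missing. This is the plainer reading and gives a small group.
- Any one of the three missing. This gives a larger group.

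On neither reading does it cover every withdrawn participant. On the plainer one, a person who gives a day 2 wash and then leaves is not caught.

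**3. What it removes.** The sentences point in different directions:
- Towards carriage only: the paragraph opens on the primary feasibility endpoint, the trigger is the nasal-wash days, and replacement serves to refill the dose-escalation denominators.
- Towards all data: the exclusion sentence has no qualifier, the heading is general, and the paragraph goes on to the other, mainly descriptive analyses. The Safety text itself refers to participants excluded from analysis and says that their reasons will be listed.

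Nothing in the article settles which is meant.

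**4. What one exclusion could do (illustration).** Assumptions: one challenged participant has an adverse event, is excluded under the rule and is replaced by someone without one; nobody else in the group has one; and the exclusion is carried into safety. The documents give no dropout or event rate, so this is not a forecast.

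Exact (Clopper–Pearson) 95% limits for x events in n:
- x = 0: lower 0, upper 1 − 0.025^(1/n)
- x = 1: lower 1 − 0.975^(1/n); upper is the p that solves (1 − p)^n + np(1 − p)^(n−1) = 0.025

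For n = 9, the upper limit at zero events is 1 − 0.025^(1/9) = 33.6%. For 1/10, the lower limit is 1 − 0.975^(1/10) = 0.3%, and the upper solves to 44.5%.

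| Group | Excluded and replaced | Everyone inoculated |
|---|---|---|
| First cohort of a dose | 0/6 (0 to 45.9%) | 1/7 = 14.3% (0.4 to 57.9%) |
| Full dose group | 0/9 (0 to 33.6%) | 1/10 = 10% (0.3 to 44.5%) |
| All challenged, maximum size | 0/27 (0 to 12.8%) | 1/28 = 3.6% (0.1 to 18.3%) |

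The intervals overlap heavily. What changes is that an event is either shown or not. If the excluded person were on sham, the comparison would shift the other way, so the direction of any bias is not fixed.

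**The case against.** The best answer is that the sentence, read in its place, is already a carriage rule. It continues a paragraph about the primary feasibility endpoint, it is triggered by absent wash data, and it exists to keep the dose-escalation counts whole. The Safety text is separate and not restricted to completers. Safety is monitored continuously, non-serious events are collected systematically, symptom logs are summarised for the DSMB, and any serious event is reported within 24 hours and pauses the study. Safety success rests on committee review of each SAE and SUSAR, not on a percentage in an analysis set. The CONSORT diagram will show inoculations and withdrawals. The Safety text plans listings, not a per-dose event rate with an interval, so the figures above illustrate an output that it does not specify. The full SAP is posted separately and may define a safety population.

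Most of this stands. A reader might infer that the adverse-event results omit all withdrawn participants, and so the people most likely to have had a problem. The documents do not support that: the rule covers only those with no day 2, 7 or 14 data, no sentence applies it to the listings, and nothing shows that those caught have more events. The provision in Safety considerations for participants who abscond or cannot be contacted ("participation in the study will be stopped and antibiotics offered as at the end of the protocol") is one way in which washes could be missed, but it says nothing about excluding data.

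What the objection does not remove is the wording. The exclusion is stated without a limit, and no other sentence restores these people to the listings. If the SAP does define an all-inoculated safety set, this sentence conflicts with it or misdescribes it.

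**Conclusion.** The point holds as a defect in a stated rule. The exclusion is not confined to the carriage endpoint and, taken literally, could remove inoculated people from the end-of-study listings of non-serious adverse events and symptoms, and from any denominators built on them. Real-time reporting of serious events and committee oversight are intact, and the context suggests that only the carriage denominator was intended.

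The likely number affected is small on the plainer reading of the trigger, but the groups are small too: one person can turn 1/10 into 0/9 at a dose, under the assumptions stated. It would go too far to conclude that the trial's safety results will be biased towards looking safe. That would require the exclusion to be applied to safety, events to be more frequent among those excluded, and the effect to fall on the challenged arm; the documents establish none of these. Severity: minor to moderate.

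**What to change.** In Statistical analysis, Missing data, limit the exclusion and replacement rule to the carriage (primary feasibility) analysis.

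In Statistical analysis, Safety, state that the adverse-event, serious adverse-event and symptom listings, and any denominators, include everyone who received any inoculation, pneumococcus or sham. They should be grouped as inoculated, should include withdrawn and replaced participants, and should use all safety data collected.

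The cost is one or two sentences, with no added participants or visits. At manuscript submission eight participants had been inoculated, at the lowest dose, and safety is to be summarised at study completion, so from that point the clarification could be made before those summaries exist. The SAP should be checked for the same wording.
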